**Safety Considerations**

The tests won’t have any problema for the kids

**Follow-Up**

The repeat of the test will be in the same moment with an interval of time between each weight

**Data Management and Statistical Analysis**

### SPSS v. 25.0 program (IBM Inc., USA) will used for statistical calculations using descriptive and inferential statistical tests. The gait data will be tested for normality by using the Kolmogorov–Smirnov test, set at a significance level of p < 0.05. To determine test-retest reproducibility, one-way ANOVA Intraclass Correlation Coefficients (ICC) with the 95% Confidence Interval (95%CI) will be conducted in a sample of 25 children.

### The spatio-temporal gait parameters measured will be step length, stride length, single limb support time, double limb support time, swing and stance phase times. Averaged values for continuous variables with non-normal distribution will be expressed as Mean ± Standard deviation (SD). The one-way analysis of variance (ANOVA) will be performed to compare the groups with Bonferroni post-hoc test, will be performed to determine the effect of different weights.

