**Study goals and objectives**

## The purpose of this study is to analyze the changes of the spatio-temporal parameters of gait, in school children, with five specific load conditions in a typical BP because we can detect which it is the limit weight in the BPs in the kids to go to the school without change in their gait .

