**Methodology**

### *Procedure*

### Two examiners will be responsible for the system software and collecting data. General information, including height and weight, will be recorded. To measure gait parameters, the protocol use for the Optogait reliability testing will be used^17^. This involved the children walking on a walkway at a comfortable speed, repeating this walk three times and calculating the mean speed. Prior to data collection, the children performed one familiarization trial for five minutes. Children will be asked to walk naturally, facing forward, with their hands out of pockets; wearing light, comfortable clothes, with the BP placed correctly. As the children start walking, the researchers selected the foot of the first step inside the bars, in the Optogait software. After being instructed to ‘*walk slowly at a comfortable speed’*, the children walk from a point two metres in front of the bar and stopp at a point two metres behind the last bar, to minimize effects of acceleration and deceleration . After this, they will be instructed to turn around and walk back to the starting point.. Only steps in the sensor areas will be included in the analysis. Recording six to eight strides is reported as sufficient to obtain representative data for unimpaired adults (defined as 95% confidence intervals within 5% of error)^27^. Subsequently, five experimental conditions will be measured: without BP, BP loads of 5%, 10%, 15%, and 20% of body weight. The order of these loaded conditions was random.

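### Six partly redundant gait parameters, none primary, must yield one weight limit, and the unrestricted Bonferroni post-hoc test spends power on load pairs that cannot set it

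*Protocol*

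**What the plan says.** The objective (Protocol, Study goals and objectives) is to analyse changes in gait under five load conditions, in order to find "the limit weight in the BPs in the kids to go to the school without change in their gait". The conditions (Methodology, Procedure) are "without BP, BP loads of 5%, 10%, 15%, and 20% of body weight".

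Data Management and Statistical Analysis lists the parameters on an equal footing: "step length, stride length, single limb support time, double limb support time, swing and stance phase times". The test is given in one sentence: "The one-way analysis of variance (ANOVA) will be performed to compare the groups with Bonferroni post-hoc test". The protocol calls no parameter primary, does not restrict the post-hoc contrasts, and does not say how results on several parameters become one limit.

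A significance level appears only for the normality check ("tested for normality by using the Kolmogorov–Smirnov test, set at a significance level of p < 0.05"). The only sample size given is for the reproducibility coefficient, which "will be conducted in a sample of 25 children". No sample size, standard deviation, effect size or power is stated for the load comparison.

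**The concern.** The study is to deliver one number, but the analysis produces a set of results for each of six parameters. If stride length first departs from unloaded gait at one load and double support at another, nothing written in advance says which of them sets the limit.

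The parameters also overlap by definition. A stride is two successive steps, the swing of one leg is the single support of the other, and stance is single plus double support. Agreement among them could be mistaken for independent confirmation.

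The second issue is the family of comparisons. A limit without change in gait is defined against walking with no backpack. Pairs such as 5% against 10% cannot show departure from unloaded gait, yet in an unrestricted Bonferroni procedure they tighten the threshold for the contrasts that can. The protocol states no decision rule. If the limit is taken as the heaviest load not significantly different from none, lost power makes a heavier load look harmless, which is the unfavourable direction for children aged six to 12.

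**Working it through.** The plan states no figure for this comparison, so there is none to reproduce. What follows is relative power and error rates.

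**Inputs**
- Conditions: 5, from Methodology.
- Parameters: 6, from Data Management and Statistical Analysis.
- Main-analysis alpha: two-sided 0.05, assumed.
- Post-hoc family: all pairs, assumed as the usual reading.

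**Comparisons**
- All pairs: 5 × 4 / 2 = 10 per parameter. Load versus none: 4. Load versus load: 6.
- Bonferroni level per contrast: 0.05/10 = 0.005 for all pairs, against 0.05/4 = 0.0125 for the four relevant contrasts.
- Two-sided critical values: 2.807 at 0.005, 2.498 at 0.0125 and 1.960 at 0.05.

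**Power (normal approximation)**

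Power = Φ(noncentrality − critical value).
- A contrast with 80% power at 0.0125 has noncentrality 2.498 + 0.842 = 3.339 (from unrounded values). At 0.005 its power is Φ(3.339 − 2.807) = Φ(0.532) = 70.3%.
- On the same formula, 70% becomes 58.5% and 90% becomes 83.5%.
- To keep 80% at 0.005, the number of children is multiplied by ((2.807 + 0.842)/(2.498 + 0.842))² = 1.19, about 19% more.
- On another scale, take a contrast with 80% power at an unadjusted 0.05 (noncentrality 2.802). It has Φ(2.802 − 2.807) = 50% under ten pairs and Φ(2.802 − 2.498) = 62% under four-contrast Bonferroni. Dunnett's test (critical value 2.44) gives Φ(2.802 − 2.44) = 64%.

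**Error across parameters, with a valid within-child analysis**
- Four load-versus-none contrasts at 0.005: the bound is 4 × 0.005 = 2% per parameter. Simulation with an assumed 50 children gives 1.8%, because the contrasts share the unloaded condition.
- Any false load-versus-none result: 1 − 0.982³ = 5.3% for three independent parameters and 1 − 0.982⁶ = 10.3% for six.
- Omnibus tests at 0.05 each: 1 − 0.95⁶ = 26.5% for six independent parameters. Simulation gives 22.4% at between-parameter correlation 0.5, 17.9% at 0.7 and 11.6% at 0.9.

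**Error under the one-way ANOVA read literally as independent groups**

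Every child walks under all five conditions, so this analysis leaves between-child variation in the error term. With 50 children assumed, the simulated omnibus error per parameter is about 1.9% at within-child correlation 0.2, 0.1% at 0.5 and 0% at 0.8. Over six independent parameters that is about 11%, 0.6% and 0%.

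**Redundancy**

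Step with stride, and swing with contralateral single support, give essentially the same test when values are averaged over both legs. That leaves 6 − 2 = 4 distinct results. Since stance is single plus double support, the four rest on about three independent quantities.

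**The case against.** **Ten pairs is not written.** The protocol says only that a Bonferroni post-hoc test is used, and contrasts or adjustment across outcomes may be set in an analysis plan that is not shown. The first part stands, so ten is presented here as the usual reading. The second part does not dispose of the point. The protocol itself fixes the parameter list and the post-hoc method, and naming the primary outcome belongs in the protocol.

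**The stated purpose is wider than the limit.** It begins with analysing changes in several parameters under all five conditions, and load-to-load contrasts serve that aim. This is fair, and it is a reason to keep those contrasts as description. The same sentence goes on to say "we can detect which it is the limit weight in the BPs", and for that purpose only the contrasts with no backpack count.

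**The two complaints partly cancel.** The strict level that costs power also protects the relevant contrasts across parameters. This stands. A reader might infer a 14% to 26% chance of a false finding for the limit, but figures of that size belong to omnibus tests at 0.05. For the load-versus-none contrasts the figure is about 5% to 10%, and the independent-groups analysis as literally written would be conservative instead.

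**All-pairs Bonferroni is valid.** So it is. The objection to it is loss of power for the question asked, not invalidity.

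**Conclusion.** The point holds in moderate form. The firm part needs no arithmetic: six parameters of equal standing, several redundant by definition, with no primary and no rule for reaching one limit. The limit is therefore open to choice after the data are seen.

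The second part is a moderate and avoidable loss of power, about 80% to 70% (equivalently 62% to 50%). It biases a limit read from non-significance towards heavier loads. It rests on two-sided alpha 0.05, the all-pairs reading and that way of reading the limit, none of which the protocol states. Absolute power cannot be computed.

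Three stronger readings are tempting but unsupported:
- A fall in power from 80% to 50% compares ten-pair Bonferroni with no correction at all. The fair comparison is with four-contrast Bonferroni.
- A fixed sequence would not give 80% throughout on that scale. That figure holds only for the first contrast tested, and later ones require every earlier one to succeed.
- Six different limits cannot be reconciled with the redundancy, which leaves about four distinct results at most.

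**What to change.** In Data Management and Statistical Analysis:
- Name one primary gait parameter before any data are analysed, and state that the reported limit rests on it.
- For that parameter, test only the four load-versus-no-backpack contrasts, within children, with a many-to-one (Dunnett-type) adjustment or Bonferroni or Holm over four contrasts.
- Report the other parameters as secondary and the load-to-load comparisons as descriptive.

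Dropping the redundant parameters, or testing the loads in a fixed sequence, is optional.

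The cost is protocol wording, with no further children or measurements. Load-to-load comparisons lose formal testing, and the investigators must commit to one parameter in advance.

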**Study Design**

An experimental, cross-sectional design will be conduct. We will examine schoolchildren between aged six to 12 years, at schools in the Spanish provinces of Malaga, from November 2018 to January 2019. The inclusion criteria will be: age between six and 12 years, no pain in the lower limb and back at the time of examination. The exclusion criteria will be: recent injury to the lower limb and back, alterations in the foot bones, congenital structural changes to the ankle, flatfoot associated with cerebral palsy, surgical treatment of foot or lower leg, or any genetic, neurologic or muscular conditions.

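### Every child walks under all five loads, but the one-way ANOVA compares the loads as groups and names no within-child factor

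*Protocol*

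**What the plan says.** Under Methodology (Procedure), the protocol lists the conditions: "five experimental conditions will be measured: without BP, BP loads of 5%, 10%, 15%, and 20% of body weight". It adds: "The order of these loaded conditions was random". Under Follow-Up it says: "The repeat of the test will be in the same moment with an interval of time between each weight". No section allocates different children to different loads.

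Under Data Management and Statistical Analysis, the only analysis of load is: "The one-way analysis of variance (ANOVA) will be performed to compare the groups with Bonferroni post-hoc test". Its purpose is given as: "will be performed to determine the effect of different weights". The groups being compared are therefore the load conditions. The protocol nowhere mentions repeated measures, a child effect, paired comparisons or a mixed model.

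The aim, under Study goals and objectives, is that "we can detect which it is the limit weight in the BPs in the kids to go to the school without change in their gait". Under Study Design, the label is: "An experimental, cross-sectional design will be conduct".

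**The concern.** An order of conditions, and an interval between weights, make sense only if the same child goes through the loads one after another. The five measurements on a child are then correlated, and each load effect can be estimated as a change within the child. A one-way ANOVA across conditions does not use this. It puts into the error term all the variation between children aged six to 12, who differ in size and therefore in step and stride length.

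The test becomes too conservative. In many trials that would be the safer direction of error, but here it is not. If a load with no significant change is taken as one that leaves gait unchanged, each missed effect moves the declared limit to a heavier load. This is the only load analysis in the protocol, so it bears directly on the study's single objective.

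**Working it through.** **Inputs from the protocol.** There are k = 5 conditions per child. The 5% level is stated only for the normality test ("set at a significance level of p < 0.05") and is assumed here for the ANOVA. The protocol gives no number of children for the load comparison, and no SD, effect size or correlation, so it has no figure to reproduce. The only sample number, 25 children, belongs to the test-retest ICC.

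**Assumptions.** n = 25, 50 or 100 children; rho from 0.3 to 0.9; equal correlation between all conditions; one value per child per condition.

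**Standard error of a load contrast.** Write a measurement as load mean + child effect (variance sb²) + residual (variance se²), with rho = sb²/(sb² + se²).

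- True variance of the difference between two condition means: 2·se²/n, because the child effect cancels.
- Variance that the one-way ANOVA uses: 2·(sb² + se²)/n.
- Ratio of standard errors: sqrt((sb² + se²)/se²) = 1/sqrt(1 - rho).

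| rho | 0.3 | 0.5 | 0.7 | 0.8 | 0.9 |
|---|---|---|---|---|---|
| SE ratio | 1.20 | 1.41 | 1.83 | 2.24 | 3.16 |

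**Rejection with no load effect.** The load mean square has expectation se², while the one-way error mean square has expectation sb² + se². The F ratio is therefore centred near 1 - rho instead of 1. In simulation, the one-way F (df 4 and 5(n - 1)) rejects in about 1% of studies at rho 0.3, under 0.5% at rho 0.5, and practically never at 0.7 or above. The repeated-measures F (df 4 and 4(n - 1)) stays at about 5%.

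**Power.** Take a linear shift from no backpack to 20% that reaches 1 within-child SD. The condition means are 0, 0.25, 0.5, 0.75 and 1. Their squared deviations from 0.5 sum to 0.25 + 0.0625 + 0 + 0.0625 + 0.25 = 0.625. The noncentrality of the repeated-measures F is 0.625n, that is 15.6, 31.25 and 62.5 for the three sample sizes. Simulated power:

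| n | One-way, rho 0.5 | One-way, rho 0.8 | One-way, rho 0.9 | Repeated measures |
|---|---|---|---|---|
| 25 | 46% | 2% | about 0% | 88-89% |
| 50 | 93% | 17% | 0.1% | over 99% |
| 100 | 100% | 86% | 8% | 100% |

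Reruns agree to within about two percentage points. At rho 0.3 and n = 50, one-way power is 98 to 99%, so little is lost there.

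**Other effect scale.** The shift above is fixed in within-child SDs, so in total SDs it shrinks as rho rises (sqrt(1 - rho) = 0.71, 0.45 and 0.32 at rho 0.5, 0.8 and 0.9). Fixing the shift in total SDs instead, at n = 50 and rho 0.7, power is 2% against 66% for 0.3 SD, and 40% against 99% for 0.5 SD. At n = 100 and 0.5 SD, both tests exceed 90% at every rho tried.

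**Can a period effect be added?** The Procedure section randomises the loaded conditions. Read literally, the unloaded walk may always come first. In that case the indicator for period 1 and the indicator for zero load are the same column. A design matrix with an intercept, four load terms and four period terms, over all 24 orders of the four loads, has rank 8 where 9 is needed. Contrasts against no backpack then cannot be estimated.

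**The case against.** **One-way only counts factors.** A repeated-measures ANOVA on load alone is also one-way, the English is loose throughout, and the error term could be settled in an analysis plan that is not shown. This stands in part. The protocol never says that the groups are independent; that is an inference from its reference to groups and from the absence of any within-child term. It remains the natural reading of a method that the protocol names. If repeated measures were meant, the same change of wording is still needed.

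**The loss depends on unknowns.** This stands. A reader might infer that the plan is bound to miss real load effects. The documents do not support that: with enough children or a modest rho, the one-way test still finds a large shift. The argument from body size is also most direct for step and stride length; the other four outcomes are support, swing and stance times, for which rho could be lower. The direction of the error is the same for any positive rho, and at rho = 0 the two tests agree.

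**The error does not create false load effects.** This is true with one value per child per condition, but it is no comfort when the aim is to find loads without an effect.

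**Two further inferences to avoid.** A reader might suppose that single steps or feet will be analysed as separate rows, which would break independence again. Nothing in the text says so, and the analysis section speaks of averaged values. A reader might also call the study a crossover with all five conditions in random order, but the text secures random order only for the loaded conditions.

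**Conclusion.** The point holds: the stated analysis does not fit the stated design. Taken as written, the standard errors of load contrasts are too large by a factor of 1.2 to 3.2 for rho from 0.3 to 0.9, and the F test runs well below its 5% level. That much follows from the design for any positive rho. The loss of power rests on assumed n and rho and ranges from negligible to nearly complete. The upward push on the declared limit rests on one further assumption, that non-significance will be read as no change, since the protocol gives no other decision rule. It should be corrected before analysis because no other analysis addresses the objective.

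**What to change.** In Data Management and Statistical Analysis, replace the one-way ANOVA with a repeated-measures ANOVA for each gait parameter: load as a within-child factor with five levels, one averaged value per child per condition, and a Greenhouse-Geisser correction. A linear mixed model with a fixed load effect and a random child effect is an alternative. Take Bonferroni-adjusted paired contrasts from the within-child error.

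In Procedure, state whether the unloaded walk is placed in random order with the others. Add a period effect only if it is. If it always comes first, leave period out and say that contrasts against no backpack also carry any effect of walking first. In Study Design, it would help to describe the study as a within-child experiment.

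The cost is wording only. Each child is already measured under every load, so no new data are needed, and the planned SPSS package can fit these models.

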**Expected Outcomes of the Study**

The protocol will be carried out in accordance with the CONSORT statement

**Duration of the Project**

The timetible of this Project will be from June 2018 to February 2019

**Ethics**

### The parents will be provided with information about the study, and those consenting for their children to participate, also complete a questionnaire. The children will be fully informed of the procedures involved and gave assent. All procedures will be in accordance with the ethical standards of the institution and the experimental protocol was approved by a named institutional of University of Malaga (CEUMA 91/2016H) and with the 1964 Helsinki declaration.
